**2. Research Summary**

Cardiac surgery with cardiopulmonary bypass is associated with a predictable incidence of myocardial and neurological dysfunction due to perioperative ischaemia that accounts for significant morbidity and mortality. Cardiac surgery is further associated with a substantial systemic inflammatory response and oxidative stress contributing to multi-organ dysfunction. Remote ischaemic preconditioning (RIPC) has been demonstrated as a novel, simple, non-invasive and inexpensive intervention in which brief ischaemia of non-vital tissue protects remote organs from a sustained episode of ischaemia. The purpose of this study is to evaluate the effects of RIPC prior to cardiopulmonary bypass on the incidence and severity of perioperative ischaemic events leading to myocardial and brain dysfunction in patients undergoing complex cardiac surgery compared to control intervention. The primary endpoint is postoperative neurocognitive dysfunction. Secondary endpoints are myocardial injury assessed by Troponin I, length of stay on the intensive care unit and total hospital stay. Furthermore, we investigate underlying pathways of RIPC in modifying the perioperative stress response with respect to myocardial tissue protein expression profile.

**3. Research Plan**

# 3.1. Introduction

# 3.1.1 Objectives

Cardiac surgery with cardiopulmonary bypass (CPB) is associated with a predictable incidence of myocardial and neurological dysfunction due to perioperative ischaemia that accounts for significant morbidity and mortality. Remote ischaemic preconditioning (RIPC) is a novel, simple, non-invasive and inexpensive intervention in which brief ischaemia of non-vital tissue protects remote organs from a sustained episode of ischaemia. The purpose of this study is to evaluate the effects of RIPC prior to CPB on the incidence and severity of perioperative ischaemic events leading to myocardial and brain dysfunction in patients undergoing complex cardiac surgery compared to control intervention.

**Key primary endpoint**

1. Postoperative neurocognitive dysfunction (POCD) after 5-7 days postoperative

**Key secondary endpoints**

1. Postoperative neurocognitive dysfunction (POCD) after 3 months
2. Incidence and severity of ischaemic events (myocardial infarction, instable angina, stroke) during hospital stay
3. Cardiac performance analysed by echocardiography
4. Cardiac performance analysed by cardiac MRI

6. Serum inflammatory biomarkers (CrP, cytokines, chemokines)

7. Myocardial tissue protein expression profile of heat shock protein-70, nitrous oxide synthetase, protein kinase C, mitogen-activated protein kinase (p38, ERK1/2), hypoxia inducible factor-1, and calcitonin gene-related protein

8. Transcriptional profiling with microarrays of leukocyte gene expression 24 hours after surgery.

**3.1.2 Background**

**Medical problem:** Cardiac surgery with CPB remains one of the most common surgical procedures, performed in about 1.5 million patients worldwide each year. Although surgical outcome has improved over time ^1^, increasingly older patients with multiple co-morbidities still remain at high risk for perioperative morbidity and mortality due to intraoperative impairment of vital organ perfusion and oxygenation. Moreover, cardiac surgery is generally associated with a predictable incidence of myocardial, neurological and renal dysfunction that accounts for significant morbidity and mortality of up to 10% depending on age, sex, co-morbidities and complexity of surgical procedures ^2-5^.

Postischaemic myocardial dysfunction after cardiac surgery is attributable to a multi-factorial aetiology, e.g. myocardial stunning, apoptosis, MI and ischaemia-reperfusion-induced injury. Clinically low cardiac output and hypotension requiring inotropic support are common findings. With respect to CABG alone, 16% of patients may experience myocardial infarction, severe ventricular dysfunction, heart failure, and/or death despite advances in surgical technique, CPB, and anaesthesia ^6^.

In addition, brain injury after CPB remains a common and serious complication ^7^. According to the ACC/AHA guidelines ^5^ postoperative neurological deficits can be classified into type 1 injuries, which are predominantly focal stroke, transient ischaemic attack, and fatal cerebral injuries in 3-5 % of patients due to macroembolism, and type 2 events, which reflect a more global/diffuse injury, with disorientation, agitation and postoperative neurocognitive dysfunction (POCD). POCD has been reported in 30 to 79% of patients at discharge and 24% to 57% at 6 months ^8^. Embolic events, changes in cerebral blood flow, global hypoperfusion, cerebral reperfusion injury, and a CPB-triggered whole body inflammatory response represent possible mechanisms for the high incidence of POCD. Elderly patients are more susceptible to cognitive impairment and stroke after cardiac surgery than others ^9^. Thus, with the increase in the percentage of elderly patients undergoing cardiac surgery, there has been a parallel increase in the incidence of stroke and POCD ^10^. Further, neurological injury negatively impacts the patient’s quality of life and health resources.

Finally, despite significant improvements in perioperative management, cardiac surgery is further associated with a substantial systemic inflammatory response and oxidative stress contributing to multi-organ dysfunction, morbidity and long-term mortality ^11^. These are triggered by the activation of leukocytes, complement, expression of adhesion molecules, cytokine release, and an increase in reactive oxygen species ^3^. Therefore, the development of strategies to control the inflammatory response continues to be the focus of extensive research.

**Remote ischaemic preconditioning (RIPC):** The most promising clinical examples for ischaemic preconditioning are angina preceding MI or transient ischaemic attacks preceding a full stroke; these preceding sub-lethal stressors are thought to enhance the tolerance of the organ to cope with the subsequent ischaemic event. However, the clinical applicability of local ischaemic preconditioning is limited by the need to induce ischaemia in the vulnerable target organ, a process that itself may aggravate organ injury and dysfunction. A more clinically relevant stimulus represents RIPC where ischaemia of non-vital tissue might protect remote organs against ischaemia-reperfusion injury, regardless of the trigger. This powerful, innate protection is mediated by recruitment of a neuronal pathway ^12^ and various neurohumoral factors such as adenosin, opioids, bradykinine, and calcitonin gene related protein ^13-16^. During the course of previous experimental investigations, brief ischaemia of the kidney, the intestine or skeletal muscle led to reduction of subsequent MI after prolonged coronary occlusion and protection against CPB-induced neural, pulmonary and myocardial damage ^17^. In humans, it has been shown that RIPC performed by transient limb ischaemia reduces ischaemia-induced endothelial dysfunction ^18^ and decreases markers of myocardial and renal injury in patients undergoing abdominal aortic aneurysm repair ^19^. In addition, RIPC modified expression of genes coding for key proteins involved in cytokine synthesis, chemotaxis, adhesion, innate immunity signalling pathways, and apoptosis in circulating human neutrophils ^20^. Finally, Hausenloy and colleagues demonstrated in a “proof-of-principle” study that RIPC reduced troponin T release by 43% as a surrogate parameter for long-term clinical outcome in the perioperative period in patients undergoing CABG ^21^. Thus, RIPC may represent an easily accessible, novel, non-invasive and inexpensive method to potentially reduce the incidence and severity of perioperative ischaemic events such as MI, stroke and ARF.

The rationale for studying RIPC in the setting of heart surgery is based on both the considerable experimental evidence that RIPC reduces myocardial ^14^ and neuronal ^22^, as wells as a few pilot trials ^19,21,23^. However, even when RIPC has been shown to reduce infarct size ^21^, this may not necessarily translate into a readily demonstrable neurological benefit, such as reduced POCD.

With respect to neurological injury, propofol and thiopental both have failed to alter outcome after cardiac surgery ^24,25^, and even therapies as potent as moderate hypothermia have been consistently shown to have little or no benefit concerning cognitive outcome ^26^. This indicates that the mechanism of CPB-induced neurological injury is more complex and cannot be sufficiently prevented with protective mechanisms offered by either hypothermia or anaesthetics alone. Thus, despite years of research, the treatment and prevention of ischaemic brain injury after cardiac surgery remains a major medical challenge. A novel method is warranted to prevent unfavourable events and to reduce POCD.

Therefore, we are now processing a prospective, randomised, blinded, single-centre study examining the effect of RIPC in patients undergoing complex heart surgery who have to deal with a predictable high incidence of myocardial and neurological injury and dysfunction that accounts for significant morbidity and mortality ^27^. Furthermore, investigating the role of RIPC in modifying the perioperative stress response at the genomic, molecular, cellular and tissue levels will improve scientific knowledge of underlying pathways.

So far, there have been no trials performed investigating RIPC in the course of complex heart surgery (CABG, aortic- or mitral valvular surgery, combined valvular and CABG surgery, and combination of ascending aortic aneurysm surgery, valvular or CABG surgery), and analysing its impact on patient’s neurological outcome. Therefore, this trial is needed now.

**3.1.3. Specific Aims**

**Major hypothesis:** RIPC results in less brain injury reflected by less neurocognitive dysfunction compared to control intervention after 5-7 days.

**Minor hypothesis:** RIPC results in less POCD compared to control intervention after 3 months, in less myocardial injury, better short-term outcome in terms of length of stay on the intensive care unit and total hospital stay. Further, we hypothesise that RIPC will modulate myocardial tissue protein expression profile of key proteins involved in organ protection in a subgroup of patients.

**3.2. Methods**

**3.2.1. Describe data collection techniques.**

**3.2.1.1. Co-workers**

-> Names in brackets indicate the role of each person involved in the project

- Dr. [name] (PM), PD Dr. med. [name] (BB), PD Dr. ret. nat. [name] (MA), [name]. med. [name] (JS); Department of Anaesthesiology and Intensive Care Medicine, University Hospital Schleswig-Holstein, Campus Kiel, Germany
- Prof. [name] (JC); Department of Heart and Vascular Surgery, University Hospital Schleswig-Holstein, Campus Kiel, Germany
- Prof. [name] (KDZ); Department of Anaesthesiology and Intensive Care Medicine, University Frankfurt, Germany

**3.2.1.2. Clinical procedures (PM, BB, JS, JC):** One-hundred eighty patients undergoing cardiac surgery (single CABG, aortic- or mitral valvular surgery, combined valvular and CABG surgery, and combination of ascending aortic aneurysm surgery, valvular or CABG surgery) will be included. Thus, study population reflects a large group of patients with increased risk of perioperative morbidity and mortality. Following exclusions criteria will be defined: Emergency cases, myocardial infarction (MI) up to 7 days and stroke up to 2 months prior to enrolment, age below 18 years, off-pump heart surgery, renal failure, drug therapy with sulfonamide and nicorandil, ejection fraction less than 30%, and previous psychiatric and neurological illness. All patients will receive standard perioperative care. The applicant (PM) will inform the patient about the nature of the trial, its aims, expected advantages as well as possible risks. Each patient must consent in writing to participate in the study. The informed consent will be signed by both patient and treating investigator.

Patients will be randomly assigned to receive either control intervention or RIPC before CPB. RIPC will be induced during anaesthesia by four 5-min cycles of right upper limb ischaemia and 5-min reperfusion using a blood-pressure cuff inflated to 200 mmHg (at least to a pressure 15 mm Hg greater than the systolic arterial pressure) measured via the arterial line ^17,23,28^. Control patients undergo sham placement of the blood pressure cuff around the upper limb with inflation to 20 mmHg. Upper limb ischaemia provided by blood-pressure cuff inflation will be performed by a single study assistant, and will be blinded to the anaesthesia team, cardiac surgeon and the patient. The anaesthesia team will perform standardised anaesthesia in all patients.

Midazolam 3.75-7.5 mg will be given orally to every patient 1 h before surgery. On arrival in the anaesthetic room, a peripheral venous and an arterial cannula will be inserted before anaesthesia. Anaesthesia will be induced with propofol (2 mg/kg), sufentanil (0.1 μg/kg), and rocuronium (0.6 mg/kg). The trachea will be intubated and mechanical ventilation will be started with oxygen with room air to achieve an end-tidal carbon dioxide tension of 4–5 kPa. Before cardiopulmonary bypass, anaesthesia will be maintained with propofol (≈ 4-6 mg/kg/h) and sufentanil (≈ 0.5-1.5 µg/kg/h). A 7F saline filled catheter will be inserted in the right internal jugular vein for determination of central venous pressure and drug administration. Arterial blood pressure, leads I and II of the electrocardiogram, and nasopharyngeal temperature will be recorded continuously. Standard CPB techniques with blood cardioplegia will be used.

Transesophageal echocardiographic variables (E/A-Ratio, left ventricular ejection fraction) will be subsequently obtained at baseline, after RIPC, and after 15 and 30 min after CPB (BB). Cardiac MRI is aimed to be performed preoperative, 5-7 days and 3 months postoperative to analyze right and left ventricular performance ^29,30^.

All patients will undergo a battery of 10 neuropsychological tests 1 day before, 5-7 days and 3 months after surgery by a blinded study nurse. In accordance with the statement of consensus on assessment of neurobehavioral outcome after cardiac surgery ^31^, the battery will include tests for motor skills, verbal memory capacity, and attention. In addition, tests will be included to assess speed and capacity of working memory, visuospatial capacity, selective and sustained attention, and information processing. Cognitive decline will be defined as a decrease in an individual’s performance of at least 20% from baseline, in at least 20% of the main variables ^32^.

**3.2.1.3. Determination of biochemical plasma markers (PM, BB, MA, KDZ):** Arterial blood samples will be collected at baseline, after CPB, and after 6, 12, 24 and 48 hours after surgery. Plasma will be obtained (centrifuged at 3000g for 5 min) and stored at -20°C until assayed. In a blinded fashion, cardiac troponin I, total creatine kinase, and inflammatory biomarkers (Cytokine multiPlex for Luminex laser; Invitrogen, Karlsruhe, Germany) will be determined using the microsphere array technique (Luminex 100 system; Luminex, Austin, USA) as previously described ^33^.

**3.2.1.4. Determination of leukocyte gene expression (MA):** In a subgroup of fifty patients (n=25 of each group), exemplarily, transcriptional profiling of leukocyte gene expression before and 24 hours after surgery will be analysed by microarrays. Blood samples will be collected into PAXgene tubes for immediate mRNA stabilization and extraction. Different gene-expression pathways involving inflammation, cellular adhesion, apoptosis and stress response will be analysed ^20,34^. Experiments will be performed in collaboration with the Institute of Clinical Molecular Biology, Kiel, Germany, using an in-house research microarray according to the guidelines of the Microarray Gene Expression Data (MGED) society ^35^.

**3.2.1.5. Determination of myocardial tissue expression profile (MA):** In a subgroup of sixty patients, exemplarily, myocardial tissue from the right atrium will be collected before cannula insertion and at the end of CPB, and stored at -20°C until assayed. Gene and protein expression profile of different mediators known to play an important role in preconditioning mechanisms, such as heat shock protein-70, nitrous oxide synthetase, protein kinase C, mitogen-activated protein kinase (p38, ERK1/2), hypoxia inducible factor-1, and calcitonin gene-related protein will be determined by standard Western blotting and real-time RT-PCR.

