**Changes of the study plan (date 01/01/2009)**

Due to technical limitations, lack of financial resources and lack of human resources the following endpoints will not be investigated:

- Cardiac performance analysed by echocardiography
- Cardiac performance analysed by cardiac MRI
- Serum inflammatory biomarkers (CrP, cytokines, chemokines)
- Transcriptional profiling with microarrays of leukocyte gene expression 24 hours after surgery

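### Atrial tissue for RT-PCR and Western blotting is to be kept at -20°C with no stated rapid freezing, stabiliser or storage limit, which puts the sensitivity of the tissue endpoint at risk

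*Protocol*

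**What the plan says.** Section 3.2.1.5 of the protocol defines the tissue work. The sample is described as "In a subgroup of sixty patients, exemplarily, myocardial tissue from the right atrium", with two collections per patient: "collected before cannula insertion and at the end of CPB, and stored at -20°C until assayed". The target is "Gene and protein expression profile of different mediators known to play an important role in preconditioning mechanisms", and these mediators "will be determined by standard Western blotting and real-time RT-PCR". The list includes HIF-1, protein kinase C, p38 and ERK1/2. The section gives no freezing method, stabiliser, inhibitor, maximum storage time or RNA quality check.

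Section 3.2.1.4 treats blood RNA differently: "Blood samples will be collected into PAXgene tubes for immediate mRNA stabilization and extraction". Section 3.2.1.3 stores plasma for troponin and the other blood markers at -20°C, in the same words as are used for the tissue.

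The key secondary endpoints list the tissue measurement as "Myocardial tissue protein expression profile of heat shock protein-70" and further proteins. The Research Summary and section 3.1.3 also speak of protein expression. Gene expression in tissue appears only in section 3.2.1.5. The page of study-plan changes dated 01/01/2009 drops "Transcriptional profiling with microarrays of leukocyte gene expression 24 hours after surgery" and the serum inflammatory biomarkers, but not the tissue endpoint. Section 3.2.2 makes the analysis of secondary endpoints exploratory.

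**The concern.** The protocol sets a storage condition for tissue that must yield both RNA and protein, and the condition is the one it uses for plasma. The premise here is general laboratory knowledge, not a figure in the documents: in tissue frozen slowly and held at -20°C without a stabiliser, enzymes that break down RNA and protein stay partly active. The loss then depends on how quickly each sample was frozen and how long it was kept.

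The last part of the minor hypothesis in section 3.1.3, that RIPC changes the myocardial protein profile, rests on these samples. Once the serum markers and the leukocyte arrays are dropped, tissue is the only one left of the three mechanistic measurements (items 6 to 8 of the key secondary endpoints). If the signal is partly lost, and lost unevenly, the trial could find no difference for reasons unrelated to biology. The samples cannot be taken again.

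**Working it through.** There is no plan figure to reproduce, and no arithmetic can yield the size of the loss: the documents give no storage time, degradation rate or RNA integrity value. The check is a comparison of passages, plus a rough look at how far sample ages could differ.

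**1. Is this a stated rule or just missing detail?** Section 3.2.1.5 names a temperature and an open-ended duration, so it is a rule. A laboratory procedure not shown could add a stabiliser, but one that stored the tissue at -80°C would contradict the protocol.

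**2. Does the protocol itself recognise the problem?**

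| Material | Section | Assay | Handling stated |
|---|---|---|---|
| Blood for RNA | 3.2.1.4 | microarray | immediate stabilisation |
| Plasma | 3.2.1.3 | troponin I, creatine kinase, cytokines | -20°C until assay |
| Atrial tissue | 3.2.1.5 | RT-PCR and Western blot | -20°C until assay |

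Tissue for RNA work gets the plasma rule, not the RNA rule.

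**3. Which measurements are exposed?**
- RNA: the RT-PCR part of section 3.2.1.5 only.
- Labile proteins such as HIF-1: the protein endpoint as listed.
- Phosphorylation of p38 and ERK1/2: only if measured. The protocol lists these kinases under expression and does not say whether total or phosphorylated forms are meant.

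**4. How many specimens?** 60 patients × 2 time points = 120.

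**5. How far could sample ages differ?** Inputs are from section 3.2.2: eight eligible patients a week, 30% consenting, stated as two to three a week, and 140 a year.
- 8 × 0.30 = 2.4 a week, so 60 / 2.4 = 25 weeks.
- At three and at two a week: 60 / 3 = 20 weeks and 60 / 2 = 30 weeks.
- At 140 a year: 140 / 52 = 2.7 a week, so 60 / 2.7 is about 22 weeks.

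If the 60 are consecutive and all samples are assayed in one batch (both are assumptions), the oldest and newest differ in age by about 20 to 30 weeks. If the 60 are spread over all 180 patients, 180 / 2.7 is about 67 weeks and 180 / 2.4 = 75 weeks. This shows only that the open-ended duration is not trivial; it does not measure degradation.

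**6. Bias or noise?** Allocation is random and the storage rule is the same for both arms, so storage age should not differ systematically between them. The two samples of one patient are taken on the same day and have the same age if assayed together. Time from excision to freezing may still vary from sample to sample. The expected effect is added variance and weaker signal.

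**The case against.** The strongest case against is that silence about a stabiliser does not show that none is used, and that such steps often sit in a laboratory procedure. That is fair, and it is why degradation is put here as a risk. It does not remove the point, because the temperature and the open-ended duration are stated.

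Second, the listed endpoint is protein, so loss of RNA does not touch it directly. This stands: the RNA argument reaches only the RT-PCR part of section 3.2.1.5. The argument about labile proteins does reach the listed endpoint.

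Third, the contrast with blood is between different materials and assays, and the blood endpoint was dropped. This also stands in part. There is no conflict between two active endpoints, but the contrast still shows that the authors knew RNA needs prompt stabilisation.

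Fourth, storage age is balanced by randomisation and shared within a patient's pair. This stands and limits the harm to noise.

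Fifth, resources are tight: endpoints were dropped for technical, financial and staffing reasons, and section 3.2.2 counts on one study team. The fix therefore has a cost, though a modest one.

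A reader might go further and infer that the endpoint is measured on degraded material, that phosphoproteins are lost, or that the 60 patients carry the information of a smaller number. The documents support none of these. They hold no integrity data and never mention phosphorylation. An effective sample size of the form 60 / (1 + r) needs a ratio r of added to biological variance that the documents do not give, and it ignores the paired samples. Nor is 25 weeks a minimum for collecting the 60 patients, as the range of 20 to 30 weeks shows.

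**Conclusion.** The concern holds in a limited form. The protocol prescribes a weak storage rule for tissue meant for RT-PCR and Western blotting. If it is followed as written, RNA and labile proteins are at risk of degradation that varies between samples. The consequence is added noise and lost sensitivity, expected to be equal in both arms, in an exploratory subgroup of 60. A null tissue result could not be separated from storage loss. The size of the loss cannot be derived from the documents.

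The primary endpoint, POCD at 5-7 days, is unaffected. The conclusion rests on the general premise that untreated tissue at -20°C does not reliably preserve RNA and labile proteins, and on there being no further preservation step outside the protocol. The point is worth correcting because this is the only mechanistic endpoint left and the change has to be made before tissue is collected.

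**What to change.** In section 3.2.1.5, replace the tissue storage clause with the following:

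- Snap-freeze each atrial sample at collection and store it at -80°C. Where there is enough tissue, the part for RT-PCR may go into RNA stabilisation solution instead.
- Assay the two samples of each patient together.
- Check RNA integrity before RT-PCR.

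If phosphorylated p38 or ERK1/2 is to be measured, say so and state how phosphorylation is preserved.

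The cost is modest consumables, -80°C space for about 120 specimens and a little handling time by the existing team. No extra biopsy or visit is needed. The protocol gives no biopsy size, so dividing a sample should remain conditional on there being enough tissue.
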